### Statistical analysis

Along more traditional statistical approaches to handle the nested data structures, Longitudinal Multilevel Modeling (MLM) will be used to analyze the (intensive) longitudinal, nested data structures [86–89]. This data-analytical approach is specifically suitable to analyze the type of data that will be collected in the proposed implementation trial. For the primary research questions for post-session and treatment outcomes, MLM with time as a repeated within-group factor and implementation condition as a between-groups factor will be used [90]. A benefit of MLM, in comparison to traditional ANOVA with repeated measures lies in the individual parameterization of the process variables over various levels (repeated measures as random variables; [89]). The main analyses will be conducted on the intention-to-treat sample and the completer data. Between-group effect sizes will be based on pre-post within control Cohen’s *d*_ppwc_ suggested by Carlson and Schmidt [91] which is a mean difference estimate that takes into account both intake values at pretreatment and differences between each treatment condition.

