### Aims of the implementation trial

Rather than contrasting increasing numbers of new overall treatment-packages, an additional approach may be to increase the understanding of fine-grained implementation strategies within already effective psychotherapies. Such research questions require the development of novel randomized clinical implementation designs that simultaneously investigate potential implementation effects along with therapist as well as patient effects [5].

This trial investigates two different implementation strategies of customizing a bona fide psychotherapy based on a well-introduced CBT-protocol for GAD [39]. The patients will be randomly assigned to two implementation conditions: (1) a systematic focus on subtle changes lasting from 7 to 20 min at the check-in phase of every psychotherapy session [61, 65]; and (2) a state-of-the-art (SOTA) check-in phase lasting several minutes mainly focused on the session goals. Potential therapists’ implementation effects will be examined based on an ABAB therapist allocation (see design). The main research questions are as follows:Practicability: Is the newly developed randomized clinical implementation trial design and particularly the therapists’ ABAB allocation practicable (ABAB crossed-therapist design), and what are the specific challenges when conducting such a structured design at the patient as well as therapist level?Post-session outcomes: Are there differences in process evaluations measured by post-session reports for the two implementation conditions? Furthermore, are early post-session outcomes predictors of symptom change and mediators of ultimate therapy outcome (e.g. [66])?Treatment outcomes: What are the differences in the treatment efficacy of the two randomized implementation conditions, (1) in dropout rates, (2) in self-reported primary and secondary outcomes [64]?Therapist effects: Are the implementation effects robust across therapists? Is there an interaction effect between potential therapists’ preferences for a particular implementation condition and outcome?

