### Assessments

For an overview of the assessments see Table 1. At intake, GAD-diagnosis and its core symptomatology is identified according to the structured interview section for GAD (DIPS; [72]). Furthermore, GAD-criteria are assessed using self-reports. The individual worries are identified using the Penn State Worry Questionnaire (PSWQ; [73]) and the Worry Domain Questionnaire (WDQ; [74, 75]). Mental disorders on Axis I are assessed using face-to-face diagnostic interviews (Strukturiertes Klinisches Interview für DSM, SKID-I; [76]).GAD-specific (primary) outcomes: The Penn State Worry Questionnaire (PSWQ; [73]) is a 16-item measure of the frequency and intensity of worry. It has considerable internal consistency (α = 0.86 in the prior trial). The Beck Anxiety Inventory (BAI; [77]) is a 21-item measure for anxiety symptoms (α = 0.92 in the prior trial).General (secondary) outcomes: The Beck Depression Inventory II (BDI-II; [78]) is a 21-item measure for depressive symptoms (α = 0.92 in the prior trial). The 9-item short version of the Symptom Check List (SCL-9; [79]) is an index for general severity (α = 0.86 in the prior trial). The short version of the Resource Self-Report Questionnaire (RES; [80]) measures various domains of individual and interpersonal strengths (α = 0.92 in the present sample).

**Table 1 Tab1:** Assessments

Measures	Assessment time					
	Recr.	Pre	S-by-S	Int.	Post	FU
Eligibility						
Structured Interview for DSM (SCID)	+					
GAD-diagnosis (DIPS)	+					
Worry Domains Questionnaire (WDQ)	+					
GAD-outcomes						
Beck Anxiety Inventory (BAI)		+		+	+	+
Penn State Worry Questionnaire (PSWQ)	+	+	1–16	+	+	+
General-outcomes						
Premature termination			1–16	+	+	+
Beck Depression Inventory (BDI)	+	+		+	+	+
Brief Symptom Inventory (BSI)		+		+	+	+
Resource potential questionnaire (RES)		+		+	+	+
Self-report process-measures						
Working Alliance Inventory - Patient (WAI-P)			1–16			
Working Alliance Inventory – Therapist (WAI-T)			1–16			
Bern Post-Session Report – Patient (BPSR-P)			1–16			
Bern Post-Session Report – Therapist (BPSR-T)			1–16			
Patients’ Therapy Expectation and Evaluation (PATHEV)		+		+		
Therapists’ preferences and outcome expectations	+ _1_					
Therapists’ self-reported focus on subtle changes			1–16			

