### Power considerations

With respect to the differences between the two comparative conditions, based on prior studies with transdiagnostic disorders [94], social phobia [95], depression [96], and GAD [64], we planned to demonstrate a medium effect size of Cohen’s *d* = 0.40 between the implementation conditions on the outcome composite. Assuming an α error level of 0.05, a statistical power (1-Beta) of 0.80, and a correlation of 0.40 between the pre- and post-measurements, the proposed study of 40 participants in each condition treated by 20 therapists is able to detect such an effect size [97].

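### The completer data share main-analysis status with the ITT sample, although dropout is itself an outcome compared between the conditions

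*Protocol article*

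**What the plan says.** The Statistical analysis section of the Protocol article assigns the analysis sets in one sentence: "The main analyses will be conducted on the intention-to-treat sample and the completer data". Nothing else in the article ranks the two sets or calls the completer analysis supportive.

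The model for the post-session and treatment outcomes is longitudinal: "MLM with time as a repeated within-group factor and implementation condition as a between-groups factor will be used". Table 1 schedules the PSWQ at every session from 1 to 16. The other self-report outcomes are taken at pre-treatment, sessions 5 and 10, post-treatment and follow-up.

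Dropout is an outcome in two places. Aims of the implementation trial asks: "What are the differences in the treatment efficacy of the two randomized implementation conditions, (1) in dropout rates", ahead of the self-reported outcomes. Table 1 lists "Premature termination" among the general outcomes, recorded from session 1 through follow-up.

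**The concern.** Whether a patient completes is known only after randomisation, and the trial sets out to test whether the condition affects it. A main analysis restricted to completers therefore conditions on something the condition may change. If one strategy loses more patients, and those who leave are doing worse, that strategy looks better among those who remain, even with no true effect.

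Giving two sets main status also leaves open which result decides if they differ. Should either be accepted as the answer, the 5% error rate would not hold even for a single endpoint. The Bias minimization section concedes a possible allegiance towards the prolonged-focus condition, which is a reason not to leave that choice open.

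**Working it through.** The article gives no dropout rate, no difference in dropout and no link between dropout and outcome, so it has no figure of its own to reproduce on this point. Its only relevant number is the planned effect, a "medium effect size of Cohen’s *d* = 0.40 between the implementation conditions on the outcome composite", used here as a yardstick. The claimed power is a separate matter. Everything else below is assumed.

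**1. Completer bias, no true effect.** Let the post-treatment outcome be standard normal, with higher meaning worse. A patient drops out when a latent propensity, correlated r with the outcome, exceeds the cut-off that gives dropout proportion p. The completer mean in an arm is then −r × h(p), with h(p) = φ(z₁₋ₚ)/(1 − p).

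- h(0.10) = 0.195, h(0.20) = 0.350, h(0.25) = 0.424
- 10% v 20%: r × (0.350 − 0.195) = 0.046 SD at r = 0.3 and 0.077 SD at r = 0.5
- 10% v 25%: r × (0.424 − 0.195) = 0.069 SD at r = 0.3 and 0.114 SD at r = 0.5

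The bias favours the arm with more dropout. With equal dropout under the same mechanism, the difference is zero.

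**2. The same scenarios in a longitudinal model.** An illustrative null simulation used 40 patients per arm, four assessment times, and a random intercept and slope. Dropouts contributed only their first two assessments. Variance components were assumed and treated as known, and therapist clustering was ignored.

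| Dropout | r | Completers (SD) | All available data (SD) | Ratio |
|---|---|---|---|---|
| 10% v 20% | 0.3 | 0.038 | 0.031 | 0.82 |
| 10% v 20% | 0.5 | 0.060 | 0.049 | 0.82 |
| 10% v 25% | 0.3 | 0.056 | 0.046 | 0.82 |
| 10% v 25% | 0.5 | 0.091 | 0.073 | 0.80 |

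Other assumed variance components bring the ratio down to about 0.70. Taking steps 1 and 2 together, completer bias is about 0.04 to 0.11 SD. Relative to d = 0.40 that is 0.038/0.40 = 10% to 0.114/0.40 = 29%. An all-available-data model keeps about 70-80% of it when the later outcomes of dropouts are missing.

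**3. Type I error if either result may be claimed.**

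- *All dropouts' outcomes obtained, dropout unrelated to outcome.* The two test statistics correlate at about the square root of the completer fraction: √0.9 = 0.949, √0.8 = 0.894, √0.7 = 0.837. The probability that at least one is significant at two-sided 0.05 is then 6.5%, 7.1% and 7.6%.
- *Dropouts contribute early assessments only.* The two tests correlate at 0.97-0.99. With equal, outcome-unrelated dropout of 10, 20 and 30%, at least one is significant in 5.5, 5.8 and 6.4% of trials. With 10% v 25% and outcome-related dropout it reaches about 7%.
- *All outcomes obtained, dropout unequal and outcome-related.* The completer test then carries bias as well. An ANCOVA simulation with 40 per arm at 10% v 20% and r = 0.5 gave 8.2% for either set and 5.0% for all randomised patients alone.

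**The case against.** The strongest reply is that the sentence may only mean that the main models, as opposed to exploratory ones, will be run on both sets, with ITT named before completers. Reporting both is customary, and a rule for discordant results commonly sits in an analysis plan that is not shown. Much of this stands. A reader might infer that the sets are co-primary, or that a favourable completer result may be headlined. The article says neither, and the either-set error rates describe a use that it neither plans nor rules out. The absence of a discordance rule is not counted here as a fault. What remains is the stated choice: one label, main, for both sets.

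A second reply is that the sizes rest on assumptions. That also stands. A reader might infer that dropout is an established consequence of the condition, but the article treats it as a question to be tested. The arms share one manual and session length and differ only in the check-in phase, so a split as wide as 10% v 25% has no support in the text. The direction is assumed too, since some patients may leave because they improved early.

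A third reply is that ranking the sets would not by itself remove the bias. This is correct, as step 2 of the working shows: most of the reduction depends on obtaining the later outcomes of dropouts.

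**Conclusion.** The point holds in a limited form. The article gives main status to a set selected on a variable that it also compares as an outcome, and it leaves open which of two main results decides. ITT patients who stop early already contribute session and intermediate assessments to the multilevel model, so nothing in the article requires completers to be a main set.

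The size is modest and conditional:

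- Completer bias is about 0.04-0.11 SD under 10% v 20-25% dropout and a correlation of 0.3-0.5, and about zero if dropout is equal and works the same way in both arms.
- Type I error is roughly 6-7% if either result could be claimed. It is up to about 7.6% if all dropouts' outcomes are obtained and dropout is unrelated to outcome, and higher only if selection bias is added.

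A reader might infer that naming ITT as decisive recovers the whole completer bias. It does not: without later data from dropouts, about 70-80% remains. This is a cheap improvement to a stated analysis choice, not a flaw that invalidates the trial.

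**What to change.** State in the Statistical analysis section that the main analysis is the ITT multilevel model using all available assessments of all randomised patients. State also that the completer analysis is a supportive sensitivity analysis that does not change the conclusion. Both analyses are kept, and the sample size is unaffected.

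Add that the post and follow-up questionnaires already scheduled in Table 1 continue for patients who stop therapy early, because most of the bias reduction depends on this.

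The cost is one or two sentences and a little follow-up effort. The completer result loses its main status.

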#### Statistical exemplification

The following analysis estimates the treatment efficacy of the two implementation conditions using random effects multilevel models [89]. To consider the variance components at each level (assessment times nested in patients and therapists), we will conduct 3-level models where the repeated assessments of the primary outcome at level 1 will be nested within patients at level 2 and therapists at level 3 (for a comparable model see e.g. [92]). Using a step-by-step approach [91], the growth models potentially will end up in a multi-predictor model to investigate the main outcome-predictors at each level simultaneously. An example of such a model is: At Level 1 (assessment level),

*PSWQ*_*ijk*_ = *π*_0*jk*_ + *π*_1*jk*_(time) + *e*_*ijk*_

where *PSWQ*_*ijk*_ is the estimated value of the Penn State Worry Questionnaire (PSWQ) within a time-specific assessment of each patient_j_ and therapist_k_; *π*_*0jk*_ represents the intake-centered intercept of the repeated PSWQ-measures within each patient; *π*_*1jk*_ (time) represents the decrease of symptoms from pretreatment up to post-treatment, and *e*_*ij*_ represents the corresponding error term.

At Level 2 (patient level),

for intercept: *π*_0*jk*_ = *ß*_00*k*_ + *ß*_01*k*_(number of comorbidities) + *r*_0*jk*_.

for time: *π*_1*jk*_ = *ß*_10*k*_ + *ß*_11*k*_(implementation condition) + *r*_1*jk*_*.*

where *π*_*0jk*_ is the estimate of the true population overall patients’ intake PSWQ and *π*_*1jk*_ is the estimation of the overall symptom reduction across the repeated assessments. Further, *ß*_*00k*_ and *ß*_*10k*_ are the estimated overall grand means of PSWQ intercept and time, and *ß*_*01k*_(number of comorbidities) and *ß*_*11k*_(implementation condition) represent the specific patients’ level predictors on intercept *π*_*0jk*_ and growth *π*_*1jk*_ respectively*.* Finally*, r*_*0j*k_ and *r*_*1jk*_ are the corresponding error terms at the patients’ level.

At Level 3 (therapist level):

*ß*_00*k*_ = *γ*_000_ + *u*_00*k*_

*ß*_01*k*_ = *γ*_010_

*ß*_10*k*_ = *γ*_100_

*ß*_11*k*_ = *γ*_110_ + *γ*_111_(therapists^’^ implementation preference) + *u*_11*k*_

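### The between-group effect size d_ppwc subtracts the whole chance intake difference; at the assumed correlation of 0.40 and equal SDs only about 40% carries forward, so it is less precise than a baseline-adjusted difference

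*Protocol article*

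**What the plan says.** The Statistical analysis section assigns the primary questions to a multilevel model with time and condition as factors. It then names a separate measure for between-group effect sizes, the pre-post d_ppwc, described as one "which is a mean difference estimate that takes into account both intake values at pretreatment and differences between each treatment condition". No regression weight, baseline covariate or standardiser is mentioned, and the formula is left to a cited source.

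The Power considerations section states "we planned to demonstrate a medium effect size of Cohen’s *d* = 0.40" "between the implementation conditions on the outcome composite" and assumes "a correlation of 0.40 between the pre- and post-measurements". The sample is "the proposed study of 40 participants in each condition treated by 20 therapists".

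The Participants section randomises patients individually.

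The example model under Statistical exemplification has two patient-level predictors, which "represent the specific patients’ level predictors on intercept" and growth respectively: number of comorbidities acts on the intercept, and implementation condition acts on the time slope only.

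**The concern.** A difference in change scores subtracts the full intake difference between arms. Under randomisation that difference is chance, and the part of it expected to persist to post is the regression slope of post on pre. With equal SDs this slope equals the correlation. A correlation of 0.40 and a subtraction weight of 1 do not fit together: the estimator over-corrects.

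What is at stake is the size of the reported effect, which readers will set beside the planned 0.40. A condition that happens to start more severe is credited with extra benefit, and one that starts milder loses some. The estimate is also less precise than the collected data allow. In addition, the example model gives both conditions the same intake mean, so the effect size and a model of that form would treat intake differently on the same data.

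**Working it through.** **Inputs from the protocol article.** 40 patients per condition, pre-post correlation r = 0.40 (stated for the outcome composite) and planned d = 0.40, all from Power considerations; individual randomisation from Participants.

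**Assumptions not in the article.** d_ppwc is the difference in mean pre-post change divided by the pooled pretreatment SD. Pre and post SDs are equal (k = SDpost/SDpre = 1; other values below). There is no dropout and no therapist variance.

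**The plan's own figure.** The article prints no standard error for d_ppwc. Its only calculation is the power statement (80 patients, "a statistical power (1-Beta) of 0.80"), and none of the variants tried returned exactly that pair. Two-sided two-sample power at 40 per arm and d = 0.40 is 37% (change score), 43% (post only) or 50% (baseline-adjusted). A two-measurement repeated-measures interaction test with f = 0.20 gives 90%. That is a separate matter; only the inputs n = 40 and r = 0.40 are used here.

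**Over-correction.** The expected post difference given intake difference b is r·k·b = 0.40b. d_ppwc subtracts b. The shift is (0.40 - 1)b = -0.60b.

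**Precision.** The variance of each difference is V × 2/40, in squared pretreatment SD units:

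| Estimator | V (k = 1) | SE |
|---|---|---|
| Change difference (d_ppwc) | 2(1 - 0.40) = 1.20 | √(1.20 × 2/40) = 0.245 |
| Post difference | 1.00 | √(2/40) = 0.224 |
| Baseline-adjusted | 1 - 0.40² = 0.84 | √(0.84 × 2/40) = 0.205 |

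d_ppwc against adjusted: 1.20/0.84 = 1.43. In general the ratio is 2(1 - r)/(1 - r²) = 2/(1 + r), which gives 1.54 at r = 0.3, 1.33 at 0.5 and 1.18 at 0.7.

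**How often it matters.** The intake difference has SE 0.224. It exceeds 0.2 SD in 37% of trials and 0.3 SD in 18%. At b = 0.3 the shift is 0.6 × 0.3 = 0.18, so a true 0.40 is expected to read 0.22 or 0.58 depending on direction. The average absolute gap between d_ppwc and the adjusted value is about 0.107.

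**Simulation (40 per arm, k = 1).** At true d = 0.40, 20,000 trials gave means of about 0.405 for all three estimators and SDs of 0.250 (d_ppwc), 0.230 (post) and 0.212 (adjusted). Per 1 SD of intake imbalance the estimates moved by -0.60, +0.41 and 0.00. A separate simulation of 40,000 trials gave |d| of at least 0.40 under no effect in 10.5% of trials with d_ppwc and 5.5% with adjustment. At true d = 0.40 the sign was wrong in 5.0% and 2.4%.

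**Sensitivity to the SD ratio, r = 0.40.**

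| k | Weight that should be used (0.40k) | Variance, d_ppwc / post | Variance, d_ppwc / adjusted |
|---|---|---|---|
| 0.8 | 0.32 | 1.56 | 1.56/0.84 = 1.86 |
| 1.0 | 0.40 | 1.20 | 1.43 |
| 1.25 | 0.50 | 1.00 | 1.00/0.84 = 1.19 |
| 1.4 | 0.56 | 0.94 | 0.94/0.84 = 1.12 |

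Over-correction persists until 0.40k reaches 1, that is, k = 2.5. The comparison with the plain post difference turns at k = 1.25 or, with equal SDs, at r = 0.5.

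**The case against.** - **The formula is inferred.** This stands as a caveat. The name and description support a change-score contrast, but not the exact standardiser, nor whether observed or model-estimated means enter. If intake means constrained to be equal were used, there would be no intake difference to over-correct.
- **A reader might infer that d_ppwc is biased.** It is not, over repeated randomisation. The shift is conditional on the imbalance observed, and the average gap of 0.107 is less than half of one standard error (0.245).
- **A reader might infer that d_ppwc is always noisier than ignoring intake altogether.** The article gives no SDs. Patients are selected at intake for meeting GAD criteria, so a post SD above the pre SD is plausible, and from a ratio of 1.25 the statement fails at r = 0.40. The loss against baseline adjustment remains at every ratio in the table.
- **The 0.40 is a planning value for the composite.** The individual scales may correlate differently, so the 43% should not be carried over to every outcome.
- **A reader might infer that the tests or primary conclusions are compromised.** They rest on the multilevel model, not on d_ppwc.
- **A reader might infer that the plan contradicts itself through the example model.** The model is offered only as an illustration, reached step by step, and it is a growth slope over repeated measurements. The two-time-point variances above do not measure its disagreement with d_ppwc. What stands is that the two handle intake differently and could differ in size and occasionally in sign.
- **An article may leave effect-size computation to the analysis plan.** It may, but this article names a specific estimator, so the point concerns a choice made and not an omission.

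**Conclusion.** The point holds as one of precision and conditional accuracy in the reported effect sizes. On the plan's own correlation for the composite, with equal SDs, 40 per arm, no dropout and no therapist variance, d_ppwc has about 43% more variance than a baseline-adjusted difference and moves by about 0.6 of any chance imbalance, in the opposite direction. The penalty shrinks to 33% at r = 0.5 and 18% at r = 0.7. It rests on reading d_ppwc as a change-score contrast. Worse precision than the plain post difference is a conditional result, limited to SD ratios below 1.25 at r = 0.40 or, with equal SDs, to correlations below 0.5. The documents support no claim of overall bias or of faulty tests. The change is worth making because it is better at almost no cost.

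**What to change.** In the Statistical analysis section, define the between-group effect size as the baseline-adjusted difference between conditions at post and at each follow-up, divided by the pooled pretreatment SD, with its confidence interval from the same model. The adjustment can come from a multilevel model with the intake value as covariate, or from one with intake means constrained equal across conditions. Keep d_ppwc as a supplementary descriptive figure, and state its formula.

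The cost is one sentence. No new data are needed, since Table 1 schedules a pretreatment assessment for every self-report outcome scale. The small downside is that the main figure is less directly comparable with studies that report d_ppwc; the supplementary figure covers that.
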